## Abstract

**Introduction:**

Warfarin has frequently been underused in older people for stroke prevention in atrial fibrillation (AF). Direct oral anticoagulants (DOACs) entered the UK market from 2008 and have been recommended as an alternative to warfarin. This study aimed to describe any changes in the prescribing of oral anticoagulants (OACs) to people aged ≥75 years in UK general practice before and after the introduction of DOACs, to examine differences in patient characteristics which may influence prescribers’ decisions regarding anticoagulation, to evaluate the time people stay on OACs and switching between OACs.

**Methods and analysis:**

A retrospective cohort study design will be used. Patients with a diagnosis of AF will be identified from the Clinical Practice Research Datalink (CPRD). The study period will run from 1 January 2003 to 27 December 2017. Patients enter the cohort at the latest date of the start of the study period, first AF diagnosis, 75th birthday or a year from when they started to contribute research standard data. Follow-up continues until they leave the practice, death, the date the practice stops contributing research standard data or the end of the study period (27 December 2017). Exposure to OACs will be defined as ≥1 prescription issued for an OAC of interest during the study period. Patients issued an OAC in the year preceding study entry will be defined as ‘prevalent users’. Patients starting on an OAC during the study period will be defined as ‘incident users’. Incidence and prevalence of OAC prescribing, patient demographics and characteristics will be described during three time periods: 2003–2007, 2008–2012 and 2013–2017. Persistence (defined as the time from initiation to discontinuation of medication) with and switching between different OACs will be described.

**Ethics and dissemination:**

The protocol for this study was approved by the CPRD Independent Scientific Advisory Committee. The results will be disseminated in a peer-reviewed journal and at conferences.

**Trial registration number:**

EUPAS29923.

Strengths and limitations of this studyThis will be a large cohort study using a validated data source which is representative of the UK population.This study will explore a number of aspects of oral anticoagulant (OAC) prescribing and will examine changes over time to show any changes in OAC prescribing practices since the introduction of direct oral anticoagulants (DOACs).Analysing differences in patient demographics, comorbidities and coprescribing between those prescribed DOACs and warfarin will provide important information for future studies aiming to compare differences in outcomes with the different OACs.This study relies on prescription data generated by general practices; therefore, we will not know if the prescribed medication was ever dispensed or taken.Warfarin dosing schedules are not recorded in the Clinical Practice Research Datalink, so duration of warfarin prescriptions will be estimated.

## Introduction

A large body of evidence has shown that vitamin K antagonists (VKAs) are safe and effective for stroke prevention in atrial fibrillation (AF), but they have frequently been underused in older people.^1^ Reasons cited by physicians as making them less likely to prescribe VKAs for a person with AF include advancing age, risk of falls, comorbidities and previous bleeding.^2^

The first direct oral anticoagulant (DOAC), dabigatran, was marketed throughout Europe and in the UK in 2008, but was not licensed for stroke prevention in AF until 2011. Since then, three additional DOACs have been licensed for prevention of stroke: rivaroxaban, apixaban and edoxaban, and these are recommended in national and international guidelines as an alternative to warfarin.^3–5^ In the UK, the National Institute of Clinical Excellence (NICE) produces technology appraisals making recommendations for new medicines. The National Health Service is legally obliged to fund those medicines recommended by NICE within 3 months of publication of the appraisal. NICE published favourable technology appraisals for dabigatran and rivaroxaban in 2012,^6 7^ apixaban in 2013^8^ and edoxaban in 2015,^9^ meaning DOACs were available across the UK from mid-2012 onwards for stroke prevention in AF.

DOACs may allay some prescribers’ concerns when deciding whether to anticoagulate their older patients: they have fixed dosing schedules and can be added to compliance aids. They have also been shown in clinical trials to have a significantly lower risk of intracranial haemorrhage than warfarin^10–13^ (a prominent concern in patients with a history of falls).^14^

Since the introduction of DOACs, the overall rate of oral anticoagulant (OAC) initiation has increased by 58%.^15^ However, it is not known whether the introduction of DOACs has changed the rates of OAC prescribing for older people (aged ≥75 years) or how patient demographics, comorbidities and concomitant prescribing affect the choice of anticoagulant prescribed in UK general practice.

This study aimed to characterise prescribing of OACs to people aged ≥75 years in UK general practice, before and after the introduction of DOACs.

### Objectives

To describe changes in the point prevalence and incidence of OAC prescribing by year prior to the introduction of DOACs (2003–2007), between the introduction of DOACs and the time they were recommended by NICE for stroke prevention in AF (2008–2012), and following NICE recommendation (2013–2017).To describe switching between OACs during the study period.To compare the characteristics of patients with AF who were newly started on OACs during each period described in objective 1 to those who were not prescribed anticoagulation in the same period.To describe persistence with DOACs compared with warfarin.

## Methods and analysis

This will be a retrospective cohort study using routinely collected healthcare data from the Clinical Practice Research Datalink (CPRD) database. The CPRD contains anonymised medical records and prescribing data from general practitioners (GPs) in primary care. It contains data for around 7% of the UK population and is representative in age, sex and ethnicity.^16^ Sociodemographic data, medical diagnoses, other clinical and test data are recorded using Read codes, and these Read codes will be used to identify patients to be included in the study and also to identify covariates as described further.

### Source population

The study period will start on 1 January 2003 and will end on 27 December 2017. The source population will consist of all patients in CPRD who have ≥1 Read codes for AF and have contributed a minimum of 12 months’ research standard data prior to entry into the cohort. To be eligible to join the study, patients need to have the following: a Read code for AF recorded during or any time prior to the start of the study period; evidence to support the diagnosis of AF, such as a second AF diagnosis at a later date, an echocardiogram or prescription for a rate limiting or antiarrhythmic medication in the 3 months before the AF diagnosis or anytime after; and age of ≥75 years at study entry.

Patients will enter the cohort at the latest of the following dates:

Start of the study period.First AF diagnosis.75th birthday.A year from the date they started to contribute research standard data.

Patients will be censored if they leave the practice, the practice stops contributing data, at their date of death or at the end of the study. For the incidence calculations and comparison of patient characteristics, patients will be censored when they are prescribed an OAC.

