#### ​Indication for prescribing

OACs are prescribed for many different indications, but only those prescribed for stroke prevention in AF will be included in this study. Patients will be excluded from the study if

They had a hip fracture or hip replacement in the 6 weeks prior to the OAC index date and only one prescription for an OAC.They had a venous thromboembolism in the 6 months prior to the OAC index date.

#### 
*​*DOAC prescription duration

The index date will be defined as the date the first prescription was issued. The expected end date will be calculated by dividing the number of tablets prescribed by the licensed number of doses per day (ie, two doses per day for dabigatran and apixaban and one dose per day for rivaroxaban and edoxaban). Where the quantity of tablets prescribed is not specified, the expected duration will be imputed from other prescriptions issued for the same product for that patient or overall for that product if patient-specific information is not available.

Patients will be classified as being continuously exposed until there is a gap of >60 days between the expected end of one prescription and the start of the next. Where there is a gap of ≤60 days between the expected end of one prescription and the start of another for the same DOAC (regardless of whether the strength prescribed changes), the gap will be filled and defined as continuous exposure. Where a subsequent prescription for the same product is issued before the expected end of the previous prescription, the prescriptions will be concatenated and the extra days will be added to the expected end date of the second prescription. A maximum of 60 additional days will be allowed per patient.

A DOAC will be defined as discontinued 60 days from the expected end date of the last prescription issued for that product.

#### 
*​*Warfarin prescription duration

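### Two eligibility rules depend on events after cohort entry: open-ended AF confirmation can distort the calendar trend, and the VTE/hip exclusion acts backward and on OAC recipients only

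*Protocol article*

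**What the plan says.** **AF confirmation (Protocol article, Source population).** Besides an AF code, a patient needs "evidence to support the diagnosis of AF, such as a second AF diagnosis at a later date, an echocardiogram" or a "prescription for a rate limiting or antiarrhythmic medication in the 3 months before the AF diagnosis or anytime after". The window has no upper limit, and a second AF code is later by definition. Cohort entry is fixed separately: "Patients will enter the cohort at the latest of the following dates", namely study start, first AF diagnosis, 75th birthday, or one year of research standard data. The date of confirmation is not on that list. All follow-up shares one end date: "The study period will start on 1 January 2003 and will end on 27 December 2017".

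**Indication exclusion (Indication for prescribing).** "Patients will be excluded from the study if" one of two conditions holds: a "hip fracture or hip replacement in the 6 weeks prior to the OAC index date and only one prescription" for an OAC, or "They had a venous thromboembolism in the 6 months prior to the OAC index date". Both count back from the OAC index date. Under OAC switching, that date falls during the study for incident users and at entry for prevalent users. A never-treated patient has none.

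**Use of the cohort (Statistical analysis).** Objective 1 divides incident users by unexposed person-time, and mid-year users by everyone in the cohort at that date. Objective 3 has a later starter supply no-OAC data in the periods before the start.

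**The concern.** A cohort should be defined by what is known at entry. Here membership depends in part on the future.

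The confirmation rule gives a patient newly diagnosed in 2003 up to 15 years to acquire evidence, and one newly diagnosed in 2017 less than a year. The same words are stricter late in the study, and calendar year is the axis on which Objective 1 is reported. Patients who die or leave before confirmation drop out of the denominators.

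The indication rule has two effects. An incident user excluded because of a later OAC start also loses the valid untreated time before it. And because the trigger is an OAC index date, a patient with the same VTE or hip event and no OAC stays in. Venous thrombosis counts towards vascular disease in the CHA2DS2-VASc definition, and a proximal femur fracture counts as a fragility fracture. Part of the Objective 3 contrast on those covariates would come from the rule itself.

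**Working it through.** The protocol states no confirmation rate, VTE or hip rate, or OAC rate, so there is no figure to reproduce. All rates below are assumptions.

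**1. Chance of inclusion by entry year.** Assume a share p0 = 0.8 or 0.9 has evidence at diagnosis, the rest acquire it at h = 0.10 or 0.20 per year, and m = 0.12 per year die or leave. With T years to study end:

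Inclusion = p0 + (1 − p0) × h/(h + m) × (1 − exp(−(h + m)T))

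| p0, h | newly diagnosed mid-2003 (T = 14.5) | newly diagnosed mid-2017 (T = 0.5) |
|---|---|---|
| 0.8, 0.10 | 88.7% | 80.9% |
| 0.8, 0.20 | 92.4% | 81.8% |
| 0.9, 0.10 | 94.4% | 90.5% |
| 0.9, 0.20 | 96.2% | 90.9% |

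**2. Effect on mid-year prevalence, the Objective 1 quantity.** Take h = 0.20. Assume 55% on treatment among patients with evidence at diagnosis and 25% among the others, constant over time, and uniform entry with B years of AF accrual before 2003. A patient without evidence at diagnosis who has been in the cohort s years at time t (years from January 2003) is confirmed by study end with probability

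1 − exp(−hs) + exp(−hs) × c(t), where c(t) = h/(h + m) × (1 − exp(−(h + m)(15 − t))).

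c(0.5) = 0.619 and c(14.5) = 0.092. Averaging over s from 0 to t + B with weight exp(−ms) gives F(t), and

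prevalence = [0.55 p0 + 0.25 (1 − p0) F] / [p0 + (1 − p0) F].

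| B (years) | F, 2003 to 2017 | p0 = 0.8 | p0 = 0.9 |
|---|---|---|---|
| 0 | 0.637 to 0.591 | 50.9% to 51.1% (+0.3) | 53.0% to 53.2% (+0.1) |
| 10 | 0.807 to 0.641 | 50.0% to 50.9% (+0.9) | 52.5% to 53.0% (+0.5) |
| 40 | 0.856 to 0.659 | 49.7% to 50.8% (+1.0) | 52.4% to 53.0% (+0.6) |

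Without selection, prevalence is 49.0% (p0 = 0.8) or 52.0% (p0 = 0.9) in every year. The spurious rise is 0.1 to 1.0 points. With h = 0.10 the same formula gives 0.2 to 1.2.

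**3. Simulation with no true trend, under other assumptions.** OAC start 0.15, exit 0.15 and OAC stop 0.10 per year; 25% of patients with AF at study start, the rest entering evenly; a share q confirmed at diagnosis, the others at rate c per year. Full link means that every OAC start itself brings a confirming record.

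| q, c | Confirmed, 2003–07 vs 2017 entrants (no link) | Prevalence bias in points, 2003 vs 2017: no link | Same: full link | Incidence ratio to truth, full link: Period 1 vs Period 3 |
|---|---|---|---|---|
| 0.9, 1.0 | 98.7% vs 93.6% | +0.0 vs +0.2 | +0.1 vs +0.2 | 1.004 vs 1.006 |
| 0.7, 0.5 | 93.1% vs 76.2% | +0.2 vs +0.9 | +0.4 vs +1.4 | 1.03 vs 1.05 |
| 0.5, 0.3 | 83.3% vs 56.7% | +0.6 vs +1.8 | +1.3 vs +3.6 | 1.09 vs 1.14 |

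With no link, the incidence ratio is about 1.00 in every period. A variant with frailty and no direct link gives 1.010 vs 0.999 (q = 0.7) and 1.029 vs 0.996 (q = 0.5).

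**4. Indication exclusion.** With start and exit rates of 0.15 per year, half of the patients start, and mean at-risk time is 1/0.30 years for starters and non-starters alike. If a fraction f of starters is removed whole:

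incidence = 15 × (1 − f)/(1 − 0.5f) per 100 person-years.

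If they are censored at that start and it is not counted, incidence = 15 × (1 − f).

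| f | Removed whole | Censored, start not counted |
|---|---|---|
| 1% | 14.93 | 14.85 |
| 5% | 14.62 | 14.25 |
| 10% | 14.21 | 13.50 |

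Losing the start from the numerator is intended. Losing the earlier person-time is not; it raises the rate by the factor 1/(1 − 0.5f), that is by 0.5%, 2.6% and 5.3%. Never-treated patients removed: none.

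**The case against.** The strongest reply is that both rules have a sound purpose and may matter little. Requiring support for an AF code reduces misclassification, and restricting to the AF indication is legitimate. If nearly all patients are confirmed around diagnosis, the trend hardly moves. The hip rule needs a single OAC prescription, and the VTE rule looks back only 6 months, so older VTE still counts in both groups. All of this stands. It bears on size, not on whether the rules select on later events.

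Four stronger readings are tempting, and the document does not support them.

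- **A spurious rise of 1.6 to 3.3 points.** Comparing the treated share of mid-2003 and mid-2017 entrants gives this (51.0% to 54.3% and 53.1% to 54.7% at h = 0.20). But Objective 1 uses everyone in the cohort at mid-year, and in 2017 that includes earlier entrants who have had years to be confirmed.
- **Immortal time that biases incidence as such.** Confirmation requires staying under observation, not staying free of OAC. Incidence moves only if confirmation is linked to OAC start, directly or, weakly, through frailty.
- **Every 2017 entrant has under a year to be confirmed.** This holds only for those newly diagnosed. Someone entering on a 75th birthday, or after one year of data, may have been confirmed long before, and evidence from the 3 months before diagnosis also counts.
- **Both rules remove treated patients only.** That is true of the indication exclusion alone. The confirmation rule mainly drops patients with short follow-up.

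**Conclusion.** The point holds for both rules.

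The confirmation rule can distort the Objective 1 calendar trend. On the illustrative rates in step 2 the spurious rise in mid-year prevalence is about 0.1 to 1.0 points. It is negligible when 90% are confirmed at diagnosis and the rest soon after, and larger when confirmation is slow and tied to OAC start. The 55% versus 25% treatment contrast is an assumption; without it the rise in step 2 is zero, although the simulation shows some shift in prevalence without any such contrast. The real size is unknown.

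The indication exclusion, as worded, deletes valid untreated person-time and earlier no-OAC contributions of incident users. It also makes the vascular disease and fragility fracture comparisons in Objective 3 asymmetric by construction. The effect on incidence is small unless such starters are common. The Discussion mentions neither rule among the limitations.

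**What to change.** **AF confirmation.** Either of two options:

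- Confirm AF within one fixed window around the first AF code, start at-risk time no earlier than the end of that window, and admit new entrants only if their window closes before 27 December 2017. A fixed window with entry left at diagnosis would still look ahead.
- Keep the present rule and repeat Objective 1 without the confirmation requirement as a sensitivity analysis.

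**Indication exclusion.** For incident users, replace exclusion from the study by censoring at that OAC index date, with the start not counted as an AF start. Exclusion may stay for prevalent users, whose index date is at entry.

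**Objective 3.** Apply the 6-month VTE restriction to no-OAC patients at their reference date for the period. The hip rule cannot be copied to them, because it requires one OAC prescription; instead, report the fragility fracture comparison with and without the starters it removes.

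**Cost.** Wording and one extra run on data already held. The fixed window loses some late-confirmed patients and a short stretch of early follow-up. OAC starts inside the window would no longer count as incident, so it should be short and its handling stated. If that loss is unwelcome, the sensitivity analysis is the lighter choice.

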### Time periods

The cohort will be analysed in three time periods:

Period 1: prior to the introduction of DOACs (2003–2007).Period 2: during the period between the introduction of DOACs and the time they were recommended by NICE (2008–2012).Period 3: following the publication of the NICE technology appraisals recommending DOACs as an option for stroke prevention in AF (2013–2017).

For each time period, patients will contribute data to either the warfarin, DOAC or no OAC group. Patients in the cohort can contribute data to more than one time period and more than one group, and may contribute differently for each objective. Patients may only contribute to the incident OAC group once with their index OAC. Any further prescriptions for different OACs would be considered to be prevalent.

### Exposure

The OACs of interest in this study are warfarin, dabigatran, rivaroxaban, apixaban and edoxaban. Warfarin is the only VKA included as it is the most commonly used VKA in the UK. Dabigatran, rivaroxaban, apixaban and edoxaban are the only DOACs licensed for the prevention of stroke in AF available during the study period.

All prescriptions for the OACs of interest that are issued following an AF diagnosis, during the study period and in the year prior to entry in to the study cohort will be identified.

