#### ​Incident and prevalent users

Exposure status will be defined at cohort entry as

‘No OAC’, where the patient had at least a year free of OAC prior to study entry and does not receive an OAC during the study period.‘Incident OAC users’, where the patient had at least a year free of OAC prior to study entry then was prescribed an OAC during the study period.‘Prevalent OAC users’ if the patient received an OAC in the year prior to study entry.

Exposure status for incident OAC users will be stratified at the start of each study period to no OAC, warfarin or DOAC.

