### Statistical analysis

#### Objective 1: to describe changes in the point prevalence and incidence of OAC prescribing by year prior to the introduction of DOACs (2003–2007), between the introduction of DOACs and the time they were recommended by NICE for stroke prevention in AF (2008–2012), and following NICE recommendation (2013–2017).

Only patients prescribed an OAC will contribute data to the incidence and prevalence calculations. For incidence, patients may only contribute to either the warfarin or the DOAC group once as they will be censored at the time they are prescribed an OAC. The point prevalence will be calculated at the midpoint of each year so will take account of switching. For prevalence, a patient could contribute to the warfarin group for some years, and the DOAC group for other years. Prescription mapping will be used to calculate the number of people with an OAC prescription that includes that time point as the numerator and the total number of people in the cohort at that time point as the denominator.

The incidence of OAC prescribing will be calculated overall and for each specific OAC. Everyone in the cohort will be considered ‘at risk’ until the time they receive their first OAC prescription. Incidence will be calculated using the number of incident OAC users as the numerator and person-time at risk for non-exposed persons as the denominator. For the person-time at risk calculation, the denominator will be truncated at the date of their first OAC prescription. Incidence will be stratified by age (75–84 and 85+) and sex.

Figure 2 illustrates how patients may contribute to the incidence and prevalence calculations throughout the study.

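### Warfarin is the only vitamin K antagonist extracted, so users of any other are handled as OAC-free and become incident users if they change to a listed drug

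*Protocol article*

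**What the plan says.** The Exposure section lists the drugs: "The OACs of interest in this study are warfarin, dabigatran, rivaroxaban, apixaban and edoxaban". The reason for leaving out other VKAs is that "Warfarin is the only VKA included as it is the most commonly used VKA in the UK". The same section limits what is extracted, in the look-back year as well as in follow-up: "All prescriptions for the OACs of interest that are issued following an AF diagnosis, during the study period and in the year prior to entry". The abstract defines exposure in the same terms: "Exposure to OACs will be defined as ≥1 prescription issued for an OAC of interest during the study period".

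Status is then assigned under Incident and prevalent users. A no-OAC patient is one where "the patient had at least a year free of OAC prior to study entry and does not receive an OAC during the study period". An incident user is one "where the patient had at least a year free of OAC prior to study entry then was prescribed an OAC during the study period".

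Under Objective 1 in the Statistical analysis section, everyone in the cohort is at risk "until the time they receive their first OAC prescription", and "Incidence will be calculated using the number of incident OAC users as the numerator and person-time at risk for non-exposed persons as the denominator". Objective 3 compares new starters with people not prescribed anticoagulation in the same period and leaves out prevalent users. Objective 4 takes all incident OAC users.

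**The concern.** That warfarin is the commonest VKA is a good reason not to analyse the others as a group of their own. It is not a reason to treat their users as untreated, and calling warfarin the most common concedes that others are in use.

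Three things are at stake:

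- **Objective 3.** Its purpose is a contrast with people who are not anticoagulated. The plan removes prevalent users to keep that contrast clean, yet leaves in the comparator anyone anticoagulated with an unlisted VKA.
- **Objective 1.** Such patients add person-time to the denominator, and their change to a listed drug is counted as a first start.
- **Objective 4.** Patients with earlier anticoagulant experience enter the persistence analysis as if newly started.

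**Working it through.** The plan states no figure on this point, so there is nothing to reproduce. The check has two parts: following one patient through the written rules, then an illustrative calculation.

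**Following a patient on another VKA**

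1. *Extraction (Exposure).* No prescription is identified, either before entry or during follow-up.
2. *Status at entry (Incident and prevalent users).* With no identified prescription, the patient passes the one-year OAC-free test.
3. *Exclusions (Indication for prescribing).* These cover recent hip fracture or replacement with a single OAC prescription, and recent venous thromboembolism. Neither removes the patient because of the other VKA.
4. *Risk set (Objective 1).* The patient contributes time at risk until a first prescription for a listed drug.
5. *Comparator (Objective 3).* In each period without a listed drug, the patient is in the no-OAC group.
6. *Change to warfarin or a DOAC.* The patient becomes an incident user and enters Objective 4.

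No section excludes, censors or separately classifies this patient.

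**Share of the no-OAC group misclassified**

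Both inputs are assumptions: a fraction q of the cohort is on another VKA, and half the cohort is classed as no OAC. The share is q / 0.5.

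- q = 0.5%: 0.005 / 0.5 = 1%
- q = 2%: 0.02 / 0.5 = 4%

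If c is that share, a reported proportion in the no-OAC group moves by c × (proportion in other-VKA users − proportion in the truly untreated). The shift is thus about 1–4% of that difference.

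**Effect on incidence**

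All inputs are again assumptions. U = 50% of the cohort is truly unexposed, f is the fraction on another VKA, λ = 10 per 100 person-years is the true initiation rate, and μ is the rate of change from another VKA to a listed drug.

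- Observed incidence = (Uλ + fμ) / (U + f)
- False share of incident users = fμ / (Uλ + fμ)
- Observed − true = f(μ − λ) / (U + f), so the sign depends only on whether μ is above or below λ

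Example with f = 1% and μ = 30 per 100 person-years: observed = (0.50 × 0.10 + 0.01 × 0.30) / 0.51 = 0.053 / 0.51 = 10.39 per 100 person-years, which is +3.9%. False share = 0.003 / 0.053 = 5.7%.

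| f | Share of at-risk group | False share of incident users, μ = 2 / 10 / 30 | Relative bias in incidence, μ = 2 / 10 / 30 |
|---|---|---|---|
| 0.25% | 0.5% | 0.1% / 0.5% / 1.5% | −0.4% / 0 / +1.0% |
| 0.5% | 1.0% | 0.2% / 1.0% / 2.9% | −0.8% / 0 / +2.0% |
| 1% | 2.0% | 0.4% / 2.0% / 5.7% | −1.6% / 0 / +3.9% |
| 2% | 3.8% | 0.8% / 3.8% / 10.7% | −3.1% / 0 / +7.7% |

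If overall prevalence is meant to cover any OAC, it is too low by f, that is 0.25 to 2 percentage points over these rows.

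**The case against.** **The OAC-free test might mean any oral anticoagulant.** The wording under Incident and prevalent users says OAC, without the qualifier used in the Exposure section, and code-list detail may sit in the full approved protocol. This does not rescue the rule. The abstract ties exposure to the listed drugs and the Exposure section ties extraction to them, so a broader test could not be run on the prescriptions that the plan identifies. This is a stated rule, not a missing detail.

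**The INR rule may catch some of these patients.** Under Warfarin prescription duration, the warfarin index date moves back to an earlier INR above 2. That is a partial safeguard at most. It would relabel time on the other VKA as warfarin, the article says INR results are recorded inconsistently, Objective 1 still ends risk time at the first prescription, and a change to a DOAC is not covered.

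**The effect cannot be shown to matter.** This stands. The only evidence of other-VKA use is the remark that warfarin is the most common, which fits a negligible share as well as a larger one. Every percentage above rests on assumed inputs.

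**The restriction is disclosed scope.** This stands in part. A reader might infer that changes from another VKA to a DOAC are wrongly lost from Objective 2. The documents do not support that, because the OAC switching section names three switch types and none starts from another VKA. Likewise, prevalence is understated only if it is presented as any-OAC prevalence; for the five named drugs it is not wrong on this account.

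**Conclusion.** The misclassification follows from the written definitions and affects the risk set and incident count of Objective 1, the comparator of Objective 3 and the entry population of Objective 4. Its size is unknown and probably small. The 1–4% of the no-OAC group is an illustration that assumes 0.5–2% other-VKA use and half the cohort without an OAC.

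A reader might go further and infer that incidence is overstated, or that the comparison before and after DOACs is distorted. The documents do not support either. The sign of the incidence bias depends on whether the change rate exceeds the true initiation rate, and neither rate is given. The bias would vary between the three periods if changes from other VKAs became more frequent once DOACs were available, but nothing in the article shows that they did. The point is a cheap improvement and does not put the study's conclusions in doubt.

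**What to change.** Add the other VKAs to the extraction and use them for classification only, not as a further analysis group:

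- A prescription for another VKA in the year before entry makes the patient a prevalent user.
- A first such prescription after entry ends at-risk time and no-OAC time. A later warfarin or DOAC prescription is then not an incident start in Objective 1 and does not bring the patient into Objective 4.
- For overall OAC prevalence, either include these users in the numerator or label the figure as warfarin or DOAC only.
- The three switch categories may stay as they are. Changes from another VKA can be reported separately if wanted.

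The cost is a short extra drug-code list in the same retrospective extract, and slightly fewer patients counted as incident or no-OAC. By construction it removes false incident starts and false at-risk time from this source, as far as the other VKA was prescribed in general practice.
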